### Primary endpoints

The primary endpoint is anatomic success after treatment of SSV insufficiency with MOCA™ or RFA at 1 year follow-up. Anatomic success is defined as occlusion of the treated vein and proven with duplex ultrasonography.

### Secondary endpoints

Post-procedural pain is evaluated using a 100-millimeter visual analog scale (VAS) during the first 2 weeks after treatment. The other secondary endpoints are initial technical success, clinical success, pain during treatment, complications and duration of the procedure. Initial technical success is defined as the ability to position the device adequately, treat the veins as planned and occlude the treated vein directly after the procedure proven by duplex ultrasonography. Clinical success is measured using the Venous Clinical Severity Score (VCSS). Complications related to the endovenous treatment, that occur within 30 days after treatment, are divided between major complications (deep venous thrombosis, pulmonary embolism, nerve injury, skin burn), minor complications (ecchymosis, superficial thrombophlebitis, hyperpigmentation, wound infection, prolonged pain >1 week) and sclerosans-related complications. Additionally, all endpoints will be evaluated at 2 and 5 years post-treatment.

### Ethical considerations

A patient, who meets the inclusion criteria, will be fully informed about the trial and provided with a patient information and informed consent form. Patients willing to participate in the study are included after signing the informed consent form. This study is conducted in accordance with the principles of the Declaration of Helsinki and Good Clinical Practice guidelines. The study protocol has been approved by the medical ethical committee in Nieuwegein, (VCMO NL42781.100.13) and the local institutional board of each participating center (LHC Rijnstate Arnhem/Commissie Lokale Uitvoerbaarheid RKZ Beverwijk).

### Safety and quality control

#### Data safety monitoring board

The Data Safety Monitoring Board (DSMB) is composed of three independent physicians: two vascular surgeons and one dermatologist. The DSMB will review safety and provide recommendations regarding the conduct of the study to the steering committee and to the accredited medical ethical committee (VCMO Nieuwegein) that approved the study protocol. An interim safety analysis will be performed after treatment and at the 4-week follow-up of the first 80 patients.

#### Adverse and severe adverse events

Adverse events (AE) are defined as any undesirable experience occurring to a participant during the study, whether or not considered related to the investigational device. This definition includes events occurring during hospital stay and up to 30 days of follow-up. Underlying disease that was present at the time of enrollment is not reported as an AE, but any increase in the severity of the underlying disease will be reported as an AE. All AEs will be monitored from the time of enrollment through the 30-day follow-up visit. Adverse events will be recorded on the case record forms. A description of the event, including the start date, end date, action taken, and the outcome will be provided.

A severe adverse event is any event leading to death, deep venous thrombosis, and neurological complications.

Data on AEs will be reported to the DSMB and to the accredited medical ethical committee via ‘Toetsingonline’ on the website of the Central Committee on Research involving Human Subjects (CCMO, http://www.ccmo.nl).

### Inclusion criteria

Inclusion criteria are: unilateral primary SSV insufficiency; C2 to C5 varicose veins; diameter of the SSV at the saphenopopliteal junction ≥3 or ≤12 millimeter; age between 18 and 80 years and written informed consent.

### Exclusion criteria

Exclusion criteria are: C6 varicose veins; previous surgery or endovenous treatment for insufficient SSV of the ipsilateral leg; oral anticoagulants; pregnancy or lactation; previous deep venous thrombosis; immobilization; contraindication or known allergy for sclerosans; coagulation disorders or an increased risk of thromboembolism; severe renal insufficiency (eGFR <30 ml/min) and/or severe liver insufficiency (leading to coagulation disorders).

### Recruitment

A total of 160 patients with primary SSV insufficiency will be included in the MESSI trial after signing informed consent (Figure 1). Before treatment begins, a vascular surgeon or dedicated physician assistant will perform a physical examination. The Clinical Etiology Anatomy Pathophysiology (CEAP) score [18] and VCSS [19] are determined. Insufficiency of the SSV is defined by duplex ultrasound as a retrograde flow >0.5 seconds after calf compression while standing [20].

**Figure 1 Fig1:**
[figure not shown]
**Flow chart.** Legend: This figure illustrates the study design. A total of 160 patients will be randomized to radiofrequency ablation or mechanochemical endovenous ablation.

After randomization, the SSV is obliterated in an outpatient setting according to the following: study arm 1: radiofrequency ablation (RFA) or study arm 2: mechanochemical endovenous ablation (MOCA™).

### Randomization

Patients will be randomized directly after inclusion by the treating vascular surgeon or physician assistant to one of the treatment arms, using a validated web-based randomization tool (Research Manager, NOVA Business Software, Zwolle, The Netherlands). The 1:1 randomization is performed by blocks of ten with stratification for participating centers.

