**Methods/Design:**

The MESSI trial (Mechanochemical Endovenous ablation versus radiofrequency ablation in the treatment of primary Small Saphenous vein Insufficiency) is a multicenter randomized controlled trial in which a total of 160 patients will be randomized (1:1) to MOCA™ or RFA. Consecutive patients with primary small saphenous vein incompetence, who meet the eligibility criteria, will be invited to participate in this trial. The primary endpoint is anatomic success, defined as occlusion of the treated veins objectified with duplex ultrasonography at 1 year follow-up. Secondary endpoints are post-procedural pain, initial technical success, clinical success, complications and the duration of the procedure. Initial technical success is defined as the ability to position the device adequately, treat the veins as planned and occlude the treated vein directly after the procedure has been proven by duplex ultrasonography. Clinical success is defined as an objective improvement of clinical outcome after treatment, measured with the Venous Clinical Severity Score (VCSS). Power analyses are conducted for anatomical success and post-procedural pain.

Both groups will be evaluated on an intention-to-treat principle.

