## Background

Varicose veins are common and symptoms range from cosmetic complaints to venous ulcers. The incidence increases with age and women are more affected than men. The majority of venous associated complaints are due to great saphenous vein (GSV) insufficiency; however, in 15% of patients, small saphenous vein (SSV) insufficiency is the main cause [1–3].

During the last decade, minimally invasive endothermal catheter modalities took over the role of surgical therapy in the treatment of small saphenous insufficiency. Surgery has been associated with high recurrence rates (25 to 60%), nerve injuries, and significant postoperative complications [4–10]. Success rates after endothermal catheter techniques, for example, endovenous laser ablation (EVLA) and radiofrequency ablation (RFA), are excellent. At 1 year follow-up, the anatomical success rate of RFA is 88% [10]. RFA is associated with fewer procedure-related symptoms, superior cosmetic results and earlier resumptions of daily activity compared to traditional surgical procedures [11, 12]. However, to perform endothermal techniques, tumescent anesthesia is essential. Furthermore, heat-induced nerve injury and post-procedural pain is inherent to endothermal ablation and can become chronic. Nerve injuries after endothermal ablation of SSV are seen in up to 11% [13].

Mechanochemical endovenous ablation (MOCA™), using the ClariVein™ system (Vascular Insights LLC, Madison, CT, USA) was introduced in Europe in 2010. Mechanical injury to the endothelium by a rotating wire at the tip of a catheter is combined with an infusion of liquid sclerosans, without the use of tumescent anesthesia. In Europe, the ClariVein™ device was registered on April 26, 2010, CE 558723.

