## Method/Design

### Study design

The multicenter randomized clinical MESSI trial is designed to compare MOCA™ and RFA in the treatment of SSV insufficiency. Patients with primary SSV insufficiency, meeting eligibility criteria, will be included at the outpatient clinics of the participating hospitals after giving written informed consent. The procedures are performed or supervised by dedicated vascular surgeons, who have performed over 20 procedures of both treatment modalities.

The following Dutch vascular centers are participating in the MESSI trial: St. Antonius Hospital Nieuwegein, Rijnstate Hospital Arnhem and Rode Kruis Hospital Beverwijk.

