### Treatment details

#### Radiofrequency ablation (RFA)

During RFA, radiofrequency energy is used to heat the vein wall of the SSV. The catheter is inserted into the vein and direct energy is delivered to the endothelium with collapsing and sealing of the vein as effect. During the MESSI study, all participating centers are using the VNUS™ ClosureFAST™ catheter (VNUS Medical Technologies, San Jose, California, USA). The VNUS™ ClosureFAST™ catheter contains a 7-cm long heating element at the end of the catheter, used for segmental ablation. Every 7-cm segment is treated during a 20-second treatment cycle in which a temperature of 120 degrees is maintained. Only the most proximal segment is treated during the two cycles [21].

The insufficient SSV is punctured distally under ultrasound-guidance and a guide wire is inserted. An introducer sheath is placed over the guide wire. Subsequently, the RFA catheter is introduced and positioned approximately 2 cm distal to the saphenopopliteal junction using ultrasound guidance. Then, tumescent anesthesia is delivered along the entire SSV to be treated. The target vein is compressed circumferentially and positioned at least 1 cm below the skin, due to the tumescence.

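### A single published block size of ten within centre lets anyone who tallies a whole centre know up to one in six allocations in advance

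*Protocol article*

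**What the plan says.** The Randomization section gives one block size and one stratification factor: "The 1:1 randomization is performed by blocks of ten with stratification for participating centers". The same section says who obtains the allocation: "Patients will be randomized directly after inclusion by the treating vascular surgeon or physician assistant to one of the treatment arms". A validated web-based tool is used.

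The Study design section names three centres and says of the operators: "The procedures are performed or supervised by dedicated vascular surgeons, who have performed over 20 procedures of both treatment modalities". The arms cannot be confused by whoever treats. For RFA, the treatment section says "Then, tumescent anesthesia is delivered along the entire SSV to be treated", whereas the Background describes MOCA as given "without the use of tumescent anesthesia".

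The article is dated 29 October 2014, and the Trial status section expects inclusion to finish in the third quarter of 2015. The Abstract adds that eligible patients are invited consecutively. The article does not describe any variation in block size, or any step to keep the size from recruiting staff.

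**The concern.** With permuted blocks of known length, past allocations carry information about the next one. Once one arm has used its five places in a block of ten, the rest of that block is settled. Before that point, the arm with fewer patients so far is the better guess. A web tool hides the list, but it does not stop anyone deducing the next entry from entries already seen.

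Here the staff who include the patient also obtain the allocation, and the operator cannot be blinded. Eligibility leaves room for case mix: the Inclusion criteria admit C2 to C5 disease and junction diameters from 3 to 12 mm, and only centre is balanced by design. If timing of inclusion or judgement about eligibility followed a predicted allocation, the arms could differ in prognosis.

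The Sample size calculation uses a non-inferiority range of 2% with 74 patients per group. One failure is 1/74 = 1.35 percentage points and two are 2/74 = 2.7, so a small shift in case mix is not small relative to that range. The main secondary endpoint is pain reported by the patient.

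**Working it through.** The article gives no figure for predictability, so there is none to reproduce.

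**Inputs from the article**
- Block size 10 and 1:1 allocation, so m = 5 per arm in each block (Randomization).
- Three centres as strata (Study design).
- 160 patients in total (Sample size calculation).

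**Assumptions**
- Every block has ten places. The article gives this one size and does not use the word fixed.
- The observer knows the size and sees every allocation in the centre.
- Patients per centre are not stated, so several splits are tried.

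**1. Certain allocations in a complete block.** An allocation is certain when one arm's quota is already used up. For block size 2m the expected number is 2m/(m + 1), a share of 1/(m + 1). With m = 5 this is 10/6 = 1.667 per block, or 16.7%. Listing all C(10,5) = 252 equally likely sequences gives the same result. By position:

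| Position in block | Probability that it is certain |
|---|---|
| 1st to 5th | 0% |
| 6th | 0.8% |
| 7th | 4.8% |
| 8th | 16.7% |
| 9th | 44.4% |
| 10th | 100% |

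**2. Whole trial.** If every block is complete, 160 × 1/6 = 26.7. Incomplete last blocks lose their most predictable positions:

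| Assumed split of 160 | Certain allocations | Share |
|---|---|---|
| 60/50/50 | 26.7 | 16.7% |
| 54/53/53 | 25.0 | 15.6% |
| 59/59/42 | 24.7 | 15.4% |
| 75/48/37 | 23.6 | 14.8% |

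**3. Guessing.** Always naming the under-represented arm is right m + (4^m / C(2m,m) − 1)/2 times per block. For m = 5: 5 + (1024/252 − 1)/2 = 6.53 of 10, or 65.3%, against 50% by chance. The expected correct guesses for other sizes are 2.83 of 4, 4.10 of 6, 5.33 of 8 and 7.72 of 12.

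**4. Partial view.** Suppose a centre's cases fall at random and evenly among operators who each count only their own. The article gives no operator numbers, so this is an assumption. By simulation the certain share falls from 16.7% to about 0.5% with two operators and below 0.1% with three.

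**5. Varying block sizes.** The simulation used 54 patients per centre and an observer who knows the set of sizes but not their order. An allocation counts as certain only if every block history consistent with the past forces it. Correct guessing is calculated for complete blocks.

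| Block sizes | Certain (simulated) | Correct guesses |
|---|---|---|
| 10 only | 15.4% | 6.53/10 = 65.3% |
| 4, 6, 8, 10 | about 1% | (2.83 + 4.10 + 5.33 + 6.53)/28 = 67.1% |
| 8, 10, 12 | about 1.4% | (5.33 + 6.53 + 7.72)/30 = 65.3% |

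Varying the size removes nearly all certainty. It does not remove better-than-chance guessing, because imbalance returns to zero at the end of every block whatever its length. Mixing in small blocks makes guessing slightly easier.

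**The case against.** The strongest reply is that one in six is a ceiling. It needs one person who follows every allocation in a centre and knows where each block starts. The article speaks of several surgeons and also lets a physician assistant randomise, so any one person may see only part of the sequence. Step 4 shows how fast certainty then disappears if tallies are not shared. This stands, and the point is worded accordingly. It does not dispose of the matter, because colleagues in one centre can pool what they know and nothing in the article prevents it.

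The article also has safeguards: consecutive invitation, consent before randomisation and a web tool. These narrow the discretion that selection needs. They leave judgement about eligibility, and how participation is presented, with the same staff.

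A reader might infer that any resulting bias would be beyond repair. The documents do not support that. CEAP and VCSS are recorded at screening, so imbalance in such measured factors can be examined and adjusted for; imbalance in unmeasured factors cannot. The primary endpoint is also duplex occlusion, assessed under a standardised imaging protocol.

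Finally, the section contradicts nothing and contains no wrong figure, and ten is less predictable than a fixed four (33% certain), six (25%) or eight (20%). That is true. This is a weakness that is cheap to remove, not an error.

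**Conclusion.** The point holds in conditional form. One stated block size within centre, published during recruitment, in a trial whose operators cannot be blinded, leaves up to 16.7% of allocations open to certain prediction by someone with a full centre tally. For the centre splits tried, that is about 24 to 27 of 160. The same person could guess about 65% correctly. Anyone with a partial view would know less, possibly far less.

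The figures assume that ten is the only size used and that the observer knows it. A reader might go further and infer that one in six allocations were in fact known to the treating surgeon, or that patients were selected. The article supports neither: it does not say that anyone sees all of a centre's allocations, and predictability is the opportunity for bias, not bias itself. No effect on the occlusion or pain comparison has been quantified.

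**What to change.** For blocks not yet opened, set the web tool to draw block sizes at random within centre, with an average no smaller than ten; 8, 10 and 12 would serve. Keep the sizes from recruiting staff, and out of site documents and publications until recruitment ends. Keep 1:1 allocation and stratification by centre.

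This brings certain allocations from about 15 to 17% down to about 1.4% for a full-tally observer and holds correct guessing at about 65%. A mix of 4, 6, 8 and 10 should be avoided, since it would raise correct guessing to about 67%.

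The cost is a setting in the existing tool and a short amendment. End-of-trial imbalance per centre may be slightly larger: the most that an unfinished block can contribute is half its size, so 6 patients with a block of 12 against 5 with a block of 10.

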### Treatment details

#### Radiofrequency ablation (RFA)

During RFA, radiofrequency energy is used to heat the vein wall of the SSV. The catheter is inserted into the vein and direct energy is delivered to the endothelium with collapsing and sealing of the vein as effect. During the MESSI study, all participating centers are using the VNUS™ ClosureFAST™ catheter (VNUS Medical Technologies, San Jose, California, USA). The VNUS™ ClosureFAST™ catheter contains a 7-cm long heating element at the end of the catheter, used for segmental ablation. Every 7-cm segment is treated during a 20-second treatment cycle in which a temperature of 120 degrees is maintained. Only the most proximal segment is treated during the two cycles [21].

The insufficient SSV is punctured distally under ultrasound-guidance and a guide wire is inserted. An introducer sheath is placed over the guide wire. Subsequently, the RFA catheter is introduced and positioned approximately 2 cm distal to the saphenopopliteal junction using ultrasound guidance. Then, tumescent anesthesia is delivered along the entire SSV to be treated. The target vein is compressed circumferentially and positioned at least 1 cm below the skin, due to the tumescence.

#### Mechanochemical endovenous ablation

The MOCA™ technique has been previously described [15]. Briefly, the ClariVein™ device is a disposable 2.6 F single-lumen catheter for infusing liquid sclerosans. A metal wire, fitted distally with a small ball, runs through the catheter (Figure 2). The motorized handle unit rotates this wire at 3,000 rpm. The purpose of this wire is to create intimal injury, to induce vasospasm and disperse the liquid sclerosans.

**Figure 2 Fig2:**
[figure not shown]
**ClariVein™ device.** Legend: **(a)** The ClariVein™ device consists of motor unit (H) and infusion catheter (C). **(b)** The dispersion tip (T) protrudes with angulated tip from catheter (CL). Acknowledgement: Figure 1 is reproduced with permission from the Journal of Endovascular Therapy. Copyright 2011. International Society of Endovascular Specialists.

The ClariVein™ catheter is introduced into the distal SSV through a 4 F micropuncture sheath. The tip of the dispersion wire is positioned 1 cm distal to the saphenopopliteal junction (SPJ). To induce spasm of the proximal SSV, the rotating wire is activated for 10 seconds. Then, the activated catheter with rotating tip is steadily withdrawn at the rate of 1 cm every 7 seconds, simultaneously dispersing liquid polidocanol (Aethoxysklerol™, KreusslerPharma, Wiesbaden, Germany). In the proximal 10 cm of the SSV 2 mL 3% polidocanol is used, the remaindering insufficient SSV is treated with 1.5% polidocanol. The total amount of used liquid sclerosans will be documented and will not exceed the allowed daily dose of 2 mg/kg/day.

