### Definitions

Anatomical success is defined as occlusion of the treated SSV segment, measured with duplex ultrasonography.

Clinical success is defined as the objective improvement of clinical outcome after treatment, measured with the Venous Clinical Severity Score (VCSS).

Initial technical success is defined as the safe placement of the device at the predefined distance from the SPJ, treatment of the SSV without technical problems and occlusion of the treated SSV directly after treatment.

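### Anatomic success is judged on whatever vein was treated: a length set after randomisation, which a sclerosant ceiling may shorten in the MOCA arm only

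*Protocol article*

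**What the plan says.** All references are to the protocol article.

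- **Primary endpoint.** Primary endpoints speaks of occlusion of the treated vein at 1 year. The Definitions section is narrower: "Anatomical success is defined as occlusion of the treated SSV segment, measured with duplex ultrasonography".
- **Failure of treatment (under Definitions).** Type 1 is a treated vein that never occluded. Type 2 is a treated vein that occluded and later recanalised, either entirely (2a) or with an open segment of more than 10 cm (2b).
- **MOCA regimen (Treatment details).** "In the proximal 10 cm of the SSV 2 mL 3% polidocanol is used, the remaindering insufficient SSV is treated with 1.5% polidocanol". The next sentence sets the limit: "The total amount of used liquid sclerosans will be documented and will not exceed the allowed daily dose of 2 mg/kg/day". No volume per centimetre is given beyond the first 10 cm.
- **RFA (Treatment details).** The vein is treated in 7-cm segments. No ceiling tied to body weight or length is stated.
- **Initial technical success.** Secondary endpoints requires "the ability to position the device adequately, treat the veins as planned and occlude the treated vein directly after the procedure". The version under Definitions asks for safe placement, treatment free of technical problems and immediate occlusion; the requirement to treat as planned is absent.
- **Sequence.** Screening includes a duplex scan (Recruitment; Table 1). Treatment follows randomisation.

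**The concern.** The unit on which the primary endpoint is scored is not fixed at entry. It is the length that the operator actually treated, decided after allocation by someone who necessarily knows which device is in use. In one arm the article also states a reason why that length might fall short of the insufficient vein.

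If a MOCA treatment is shortened, the untreated remainder fits neither failure type, because both types concern vein that was treated. The patient can be a full anatomic success with insufficient vein still open. An RFA patient with a similar open length that had been treated and then recanalised is a failure. In a non-inferiority comparison, a scoring rule that can overlook open vein mainly in the experimental arm works towards the conclusion that the trial hopes to reach.

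**Working it through.** The article states no total dose, treatable length or minimum weight, so there is no figure of its own to reproduce on this point. The check asks when the ceiling could shorten a treatment, and how such a patient would then be scored.

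**Inputs from Treatment details (MOCA)**
- Proximal 10 cm: 2 mL of 3%, i.e. 2 mL × 30 mg/mL = 60 mg, at 2 mL / 10 cm = 0.2 mL/cm.
- Remaining insufficient vein: 1.5%, i.e. 15 mg/mL, volume not stated.
- Ceiling: 2 mg/kg × weight *w*.

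**Assumptions, not in the article**
- Distal rate *r*, shown for 0.1, 0.2 and 0.3 mL/cm.
- Body weights of 50, 60 and 70 kg.

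**Step 1. The fixed part alone.** 60 mg reaches the ceiling only at 60 / 2 = 30 kg. The proximal dose by itself creates no practical conflict.

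**Step 2. Volume of 1.5% left = (2*w* − 60) / 15.**
- 50 kg: (100 − 60) / 15 = 2.67 mL
- 60 kg: (120 − 60) / 15 = 4.00 mL
- 70 kg: (140 − 60) / 15 = 5.33 mL

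**Step 3. Longest vein treatable within the ceiling = 10 + (2*w* − 60) / (15*r*) cm.**

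| Assumed distal rate | 50 kg | 60 kg | 70 kg |
|---|---|---|---|
| 0.1 mL/cm | 36.7 | 50.0 | 63.3 |
| 0.2 mL/cm | 23.3 | 30.0 | 36.7 |
| 0.3 mL/cm | 18.9 | 23.3 | 27.8 |

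The row at 0.2 mL/cm continues the only rate that can be read from the article.

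**Step 4. When the untreated remainder would itself exceed 10 cm.** Add 10 cm to each entry. At 0.2 mL/cm the insufficient vein must be longer than 33.3, 40.0 or 46.7 cm (50, 60, 70 kg). At 0.1 mL/cm it must exceed 46.7, 60.0 or 73.3 cm; at 0.3 mL/cm, 28.9, 33.3 or 37.8 cm.

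**Step 5. Scoring side by side.** Take an illustrative 50 kg patient with 35 cm of insufficient vein and 0.2 mL/cm.
- MOCA: 35 − 23.3 = 11.7 cm is left untreated. If the treated 23.3 cm is occluded at 1 year, the Definitions wording gives anatomic success.
- RFA: the whole 35 cm is treated. If 11.7 cm recanalises, the patient is a type 2b failure.

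The open length is the same and the outcomes are opposite. At 0.1 mL/cm the same MOCA patient could be treated in full (36.7 cm > 35 cm), and the difference disappears.

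**Step 6. Whether anything else catches it.** Intention-to-treat analysis decides the arm in which a patient is counted, not the length of vein that is scored. Initial technical success under Secondary endpoints would record the shortfall; under Definitions an uneventful but shortened treatment may pass. A secondary endpoint does not in any case alter the primary one.

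**The case against.** The strongest reply is that the regimen is not fully fixed. Beyond 10 cm the article gives a concentration and no volume, so the ceiling limits an unspecified quantity and the two instructions do not strictly contradict each other. The article calls its own description brief and cites an earlier account of the technique; infusion rates and the handling of a reached ceiling may stand in the full protocol. This is correct. It removes any claim that eligible patients exist who cannot be treated as planned. A reader might infer this from the lack of a weight or vein-length criterion, but the documents support only that it may happen.

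The endpoint wording also applies to both arms, and RFA may be shortened for other reasons. That stands too: the one-sidedness lies in the stated ceiling, not in the definition.

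Two further inferences are tempting and should be resisted.
- **That two misclassified MOCA patients use up the 2% margin.** Two of 74 is 2.7 points, but nothing in the article supports that count. The margin is tested against the uncertainty of the difference, with 97% versus 88% assumed in planning; it is not an allowance of patients.
- **That technical success is confounded with body weight.** Weight is a baseline variable balanced in expectation by randomisation. If a ceiling prevents treatment as planned, that is a genuine property of MOCA, and counting it as technical failure is right.

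None of this answers the core point: the primary endpoint is scored on a length chosen after randomisation, and no stated rule counts insufficient vein left untreated.

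**Conclusion.** The point holds as a defect in the endpoint definition. Both wordings of the primary endpoint rest on what was treated, and the failure types do not cover vein that was never treated. The MOCA ceiling supplies a concrete, one-sided route by which treated and insufficient length may differ, in a direction that can favour non-inferiority.

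The size is conditional. At an assumed 0.2 mL/cm the ceiling matters beyond about 23 cm at 50 kg and 30 cm at 60 kg; at 0.1 mL/cm, beyond about 37 and 50 cm. The article gives neither the distal rate nor the distribution of weight and vein length, so the number affected cannot be derived and may be small. One patient wrongly scored as a success moves the MOCA rate by 1/74 = 1.4 points. That shows sensitivity; it is not an estimate of bias.

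A reader might conclude that such patients should be screened out. The documents do not support that step: the check would need the unstated distal volume, would be a clinical rule tied to a dose limit, and would remove the very patients in whom MOCA is limited. The change is worth making because it is cheap and protects the primary comparison even if shortened treatments prove rare.

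**What to change.** 1. At the screening duplex, before randomisation, record the insufficient SSV segment planned for treatment, by one rule that does not depend on the arm.
2. In Primary endpoints and Definitions, use one wording and judge anatomic success in both arms on that planned segment.
3. Under Failure of treatment, apply the existing criteria, including the threshold of more than 10 cm open, to planned vein that was never treated as well as to vein that recanalised.
4. Make the two definitions of initial technical success agree on whether treatment as planned is required.
5. The sponsor should reconcile the MOCA regimen with the ceiling stated beside it. No dose, volume or eligibility rule is proposed here.

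The cost is some wording and one or two case report form fields, taken from a scan that is already scheduled. The reported success rate may come out slightly lower.
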